## Abstract

**Introduction::**

Patients with femur fracture benefit from early surgery. Recent reports suggest that regional anesthesia may be superior to general anesthesia in these patients. Early surgery under spinal anesthesia could be performed safely by determining platelet function in patients receiving antiplatelet agents.

**Methods::**

Multicenter, randomized, open-label, parallel clinical trial expected to include 156 patients ≥ 18 years of age under chronic treatment with antiplatelet agents who develop a proximal femur fracture. Exclusion criteria: presence of multiple or pathological fractures, current treatment with vitamin K antagonists or new oral anticoagulants, and congenital or acquired coagulopathy.

Patients will be randomized to either

The primary endpoint is time (hours) from admission to surgery. Secondary endpoints include: platelet function; postoperative bleeding; medical-surgical complications; perioperative and 1-year mortality; quality of life; length of hospital stay; cost-effectiveness; and cost-utility. Follow-up assessments will be performed during hospital admission and at 1, 6, and 12 months after surgery.

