### Study design

2.1

Multicenter, randomized, open-label, parallel clinical trial of patients receiving chronic antiplatelet therapy admitted to the emergency department with a femoral fracture. All study participants will undergo platelet function testing and those with more than 80,000 functional platelets will be randomized to either early surgery with neuraxial anesthesia or delayed surgery with neuraxial anesthesia performed in accordance with the antiplatelet activity time of the specific antiplatelet drug (3 days for aspirin 300 mg/day and triflusal 600 mg/day; 5 days for clopidogrel and ticagrelor; 7 days for prasugrel, and 10 days for ticlopidine).

Recruitment started in September 2017 and will continue until December 2019. The last follow-up visit for the final patient included in the study will be in December 2020. To date, 81 patients have been included.

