#### Secondary outcomes

2.4.2

Clinical: postoperative bleeding, complications associated with the surgical procedure and surgical wound, medical complications during admission, perioperative mortality and mortality at 1 year, quality of life (EQ-5D-5L generic questionnaire) assessed preoperatively and postoperatively at days 5 and 30 and months 6 and 12.

Costs: length of hospital stay, surgery-associated direct health costs, laboratory tests, medications, consumables, complementary diagnostic tests, resources required to treat perioperative complications, cost associated with rehabilitation, consultations with specialists, and primary care visits after hospital discharge and during follow-up.

A subgroup analysis of 20 consecutive patients from one of the participating centers will be performed to determine the correlation between 2 platelet function systems (PlaTeLet work [PTLwork] versus the conventional Platelet Function Assay [PFA-100 system]).

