#### Patient follow-up

2.4.3

Follow-up visits will be conducted during hospitalization, and postoperatively by phone at months 1, 6, and 12.

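### Follow-up visits and EQ-5D-5L are scheduled from surgery, whose timing is what the arms differ in, so early assessments fall at different times since randomisation

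*Protocol article*

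**What the plan says.** The visit schedule is tied to surgery in two places. The abstract's Methods paragraph has "Follow-up assessments will be performed during hospital admission and at 1, 6, and 12 months after surgery", and section 2.4.3 repeats it: "Follow-up visits will be conducted during hospitalization, and postoperatively by phone at months 1, 6, and 12". Section 2.4.2 has EQ-5D-5L "assessed preoperatively and postoperatively at days 5 and 30 and months 6 and 12"; the day of the preoperative assessment is not given.

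The other clinical outcomes in section 2.4.2 use other windows. Bleeding is postoperative only. Medical complications are counted over the hospital stay ("medical complications during admission"). Mortality is listed as "perioperative mortality and mortality at 1 year", with no starting point.

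Section 2.7 has patients selected on the day of admission, then consented and randomised, so surgery comes after randomisation. Section 2.8.1 schedules experimental patients within 24 hours once platelet function is adequate. Under section 2.8.2 controls wait for the drug-specific time, which section 2.1 gives as "3 days for aspirin 300 mg/day and triflusal 600 mg/day; 5 days for clopidogrel and ticagrelor; 7 days for prasugrel, and 10 days for ticlopidine".

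The primary endpoint (section 2.4.1) and the cost-effectiveness measure (section 2.9.2) both start at admission.

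**The concern.** A time origin should be the same for both arms and should not be altered by the treatment. Surgery fails this here, because moving the date of surgery is what the strategy does. Four consequences follow.

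- Early quality of life is compared at different times since fracture and randomisation, and these scores feed the early part of the QALY calculation.
- A control patient's preoperative EQ-5D-5L may be taken after days of waiting. It would then be a post-randomisation measure that already carries part of the effect of delay.
- Medical complications are counted over a stay that the article itself expects to be shorter after early surgery (abstract, potential impact), so the arms are observed for different lengths of time.
- Patients who die before surgery have no postoperative assessment, and the longer wait leaves more room for this in controls.

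At stake is the interpretation of the secondary comparisons of early quality of life, complications, mortality and cost-utility. The article's rationale is that delay does harm, so the waiting period should be inside the comparison on equal terms.

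**Working it through.** **Reproducing the plan's figure.** Inputs from section 2.9.1: SD 3.17 days, difference 1.5 days, two-sided alpha 0.05, power 80%, 10% loss. Per arm, n = 2 × (1.960 + 0.842)² × (3.17/1.5)² = 70.1. Dividing by 0.9 gives 77.9, hence 78 per arm and 156 in total, as stated. (Rounding up to 71 before allowing for losses gives 79 per arm, 158 in total.) The endpoint behind this calculation starts at admission, so the present point leaves it unchanged.

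**Visit timing.** Days since admission = wait + scheduled postoperative day. Control waits are 3, 5, 7 or 10 days (section 2.1). The experimental wait is taken as 1 day (section 2.8.1).

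| Postoperative visit | Experimental | Control, by wait of 3 / 5 / 7 / 10 days | Gap as share of interval |
|---|---|---|---|
| Day 5 | 6 | 8 / 10 / 12 / 15 | 40% to 180% |
| Day 30 | 31 | 33 / 35 / 37 / 40 | 7% to 30% |
| Month 6 (182.5 days) | 183.5 | 185.5 / 187.5 / 189.5 / 192.5 | 1.1% to 4.9% |
| Month 12 (365 days) | 366 | 368 / 370 / 372 / 375 | 0.5% to 2.5% |

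The gap is 2, 4, 6 or 9 days. These are upper values for each drug: under section 2.8.1 an experimental patient whose platelet function is not adequate is retested and may end up waiting the full drug-specific time, and the gap then shrinks or disappears. The article gives no drug mix, so no average gap can be calculated.

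**Deaths during the wait.** Assume a constant hazard and 30-day mortality m. The probability of death in w days is 1 − (1 − m)^(w/30), multiplied by 78 patients. The introduction gives m as up to 10%, for postoperative mortality; 5% is an assumed lower value.

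| 30-day mortality | 1-day wait | 3 days | 5 days | 7 days | 10 days |
|---|---|---|---|---|---|
| 10% | 0.27 | 0.82 | 1.36 | 1.89 | 2.69 |
| 5% (assumed) | 0.13 | 0.40 | 0.66 | 0.93 | 1.32 |

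Each control figure supposes that all 78 controls have that wait.

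**One-year mortality, if it were counted from surgery.** Take 10% mortality at 30 days and 18% to 33% at one year (introduction), with a constant hazard over the remaining 335 days: h = −ln[(1 − m₁)/0.9]/335. A shift of s days at the end of follow-up changes the result by (1 − m₁)(1 − e^(−hs)). For m₁ = 18% and s = 2 this is 0.05 percentage points; for m₁ = 33% and s = 9 it is 0.53. The end-of-follow-up shift is therefore small. What matters for mortality is whether deaths before surgery are counted.

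**The case against.** A reader might infer that mortality is timed from surgery, that events during the wait are lost, and that controls gain immortal time which hides the harm of delay. The article does not support this.

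- Only the visit schedule is postoperative; the origin of one-year mortality is not stated.
- Events before surgery are recorded. Follow-up covers the hospital stay, medical complications are counted throughout it, any death is a serious adverse event (section 2.10), and the intention-to-treat set keeps everyone randomised (section 2.9.2).
- Immortal time is the wrong label. A clock starting at surgery would exclude the wait rather than credit it as event-free survival; the issue would be selection of patients who reach surgery.

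A reader might also divide 2.7 by the 7.8 control deaths expected at 10% of 78 and conclude that about 35% of 30-day control deaths are at issue. That needs the ceiling mortality, a constant hazard applied to a pre-operative period, and every control on a 10-day wait. At the planning difference of 1.5 days the same formula gives 1 − 0.9^(1.5/30) = 0.5%, or about 0.4 deaths per 78.

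Nor does the article start QALYs or costs at surgery. There is a preoperative EQ-5D-5L, and length of stay is costed. A day-5 postoperative score is also a reasonable recovery measure, since a score at a fixed early day from admission would set operated patients against controls still waiting. Finally, morbidity and mortality are declared exploratory in the discussion.

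All of this stands, and it narrows the point. It does not remove the treatment-dependent origin of the early EQ-5D-5L assessments, the unfixed baseline day or the arm-dependent complications window.

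**Conclusion.** The point holds in a limited form. Visits and postoperative EQ-5D-5L are anchored to an event after randomisation that the intervention moves. By designed waits the misalignment is 2 to 9 days: large at day 5, moderate at day 30, negligible at 6 and 12 months. Baseline EQ-5D-5L and the complications window can also depend on arm.

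The number of patients who would die before any postoperative assessment is small: 0.4 to 2.7 of 78 controls against 0.1 to 0.3 of 78 in the experimental arm. This rests on a constant hazard, 30-day mortality of 5% (assumed) to 10% (the article's upper figure), uniform control waits of 3 to 10 days, and a 1-day experimental wait.

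The article does not show that mortality or QALY results will be biased, because it does not fix where those clocks start. The primary endpoint and the sample size are unaffected. The change is worth making because it is cheap and gives both arms one origin.

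**What to change.** - **Mortality:** analyse 30-day and one-year mortality from randomisation in all randomised patients, including deaths before surgery.
- **Complications:** count them over a fixed 30-day window from randomisation in both arms.
- **EQ-5D-5L:** take the baseline at admission. Keep the postoperative day-5 score as a descriptive recovery measure.
- **QALYs and costs:** calculate both over 12 months from randomisation, using actual assessment dates.
- **Remaining calls:** schedule months 1, 6 and 12 from randomisation.

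**Cost.** Calls move by up to about 10 days. Admission and surgery times are already among the key variables collected (section 2.7), and deaths are notified, so mortality can be re-timed for patients already enrolled. EQ-5D-5L interviews already held among the 81 patients included so far cannot be moved, only placed at their actual dates; the same applies to a baseline taken late. A 30-day window from randomisation also contains fewer postoperative days for controls (20 after a 10-day wait, against 29 after a 1-day wait). That is appropriate when comparing strategies, and the outcomes defined after surgery can still be reported descriptively beside it. The sample size does not change.

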**Potential impact of the study::**

The determination of platelet function at admission to the emergency department in patients with femoral fracture receiving antiplatelet therapy may permit earlier surgery under spinal anesthesia, thus shortening the hospital stay and reducing the risk of complications. These advantages associated with early surgery could positively impact patient well-being and also reduce treatment-related healthcare costs.

**Ethics and dissemination::**

The study has been approved by the ethics committees at all participating centers. Their results will be disseminated in congresses and published in peer reviewed journals.

## Introduction

1

Femoral fractures in elderly patients are the most common cause of admission to Orthopaedic Surgery and Traumatology departments. Proximal femoral fractures account for approximately 42–50% of all fractures in the elderly population.^[1]^ Postoperative mortality rates in the first 30 days can be as high as 10% and range from 18–33% in the first year. Several patient-related variables—including older age, males, dementia, and frailty—are associated with higher mortality rates.^[2–6]^ The annual cost to the health care system of treating femoral fractures is non-negligible, primarily due to high morbidity and mortality rates.^[7,8]^

Clinical guidelines recommend that surgery be performed, if feasible, within the first 48 hours after fracture in order to reduce perioperative complications and in-hospital morbidity and mortality.^[9,10]^ Although studies have shown that early surgery is beneficial for patients on chronic antiplatelet therapy,^[11]^ these patients must undergo general anesthesia because neuraxial anesthesia is contraindicated.^[12–15]^ The choice of anesthetic technique in patients with femoral fracture is controversial due to influence of the anesthetic technique on postoperative morbidity and mortality. Based on recent data, neuraxial anesthesia yields lower in-hospital mortality rates and shorter hospital stays than general anesthesia in patients with femoral fracture.^[16,17]^ However, more evidence is needed to definitively resolve this debate. In this regard, 2 clinical trials are currently underway to compare these 2 anesthetic techniques.^[18,19]^

Some clinical guidelines recommend platelet function testing to shorten the time from admission to surgery in patients who undergo neuraxial anesthesia.^[20,21]^ In patients receiving chronic antiplatelet treatment, the use of these tests to determine the number of functional platelets is crucial to ensure that early surgery with neuraxial anesthesia can be performed safely.

In this context, we have designed a randomized clinical trial to evaluate the safety and efficiency of a therapeutic strategy involving preoperative determination of platelet function in patients with femoral fracture receiving chronic antiplatelet treatment. The main objective of this trial is determined whether this strategy, designed to reduce the time from admission to surgery under spinal anesthesia, provides any benefits compared to a conventional strategy based on delayed surgery after discontinuation of antiplatelet therapy.

## Methods

2

The study protocol (version 3, code IIBSP-PLA-2016–86) was developed in accordance with the SPIRIT recommendations for interventional trials.^[22]^ The present randomized controlled trial was approved by the ethics committees of all participating centers and registered at clinical trials.gov (NCT03231787).

### Study design

2.1

Multicenter, randomized, open-label, parallel clinical trial of patients receiving chronic antiplatelet therapy admitted to the emergency department with a femoral fracture. All study participants will undergo platelet function testing and those with more than 80,000 functional platelets will be randomized to either early surgery with neuraxial anesthesia or delayed surgery with neuraxial anesthesia performed in accordance with the antiplatelet activity time of the specific antiplatelet drug (3 days for aspirin 300 mg/day and triflusal 600 mg/day; 5 days for clopidogrel and ticagrelor; 7 days for prasugrel, and 10 days for ticlopidine).

Recruitment started in September 2017 and will continue until December 2019. The last follow-up visit for the final patient included in the study will be in December 2020. To date, 81 patients have been included.

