#### Inclusion criteria

2.3.2

Study inclusion criteria:

(1)adults (male or female) ≥ 18 years of age;(2)diagnosis of femoral fracture; and(3)receiving treatment with antiplatelet agents (acetylsalicylic acid [ASA] > 100 mg/d; triflusal > 300 mg/d; clopidogrel; prasugrel; ticagrelor; or ticlopidine) at admission to the emergency department.

Written informed consent will be obtained from all patients.

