#### Exclusion criteria

2.3.3

Exclusion criteria: presence of multiple or pathological fractures, current treatment with vitamin K antagonists or new oral anticoagulants, and congenital or acquired coagulopathy.

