### Blinding

2.6

Necessarily, the patients and researchers will know which intervention they have been allocated. However, to avoid influencing the timing of the surgical procedure, the investigators will be blinded to the platelet function status in the control group.

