### Implementation and data collection

2.7

Figure 1 describes the patient recruitment process and the study plan. A competitive recruitment process will be used; thus, no predetermined limit to the total number of patients per center has been established. Patient selection will be performed on the day of admission to the hospital emergency department. Researchers will first verify that the patient meets the study inclusion criteria. The patient will then be informed about the clinical trial and asked to participate. Patients who agree to participate will be enrolled in the study after signing the informed consent form. Next, they will be randomized to one of the 2 study groups.

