#### Experimental intervention

2.8.1

At emergency room admission, the antiplatelet medication will be discontinued and platelet function will be determined. In patients with >80,000 functional platelets, the surgery will be scheduled within the next 24 hours. However, if the level of functional platelets is <80,000, then the platelet assay will be performed once per day for the next 2 days or until normalized (whichever occurs first): surgery will be performed within 24 hours after normalization. If the number of functional platelets has not normalized after 3 days, surgery with neuraxial anesthesia will be scheduled in accordance to the margin of safety time established for the specific antiplatelet medication.

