#### Control intervention

2.8.2

Antiplatelet therapy will be discontinued at admission to the emergency room. Surgery with neuraxial anesthesia will be performed in accordance with the established safety time for the antiplatelet drug. Platelet function will be determined the day before surgery but the results will not be revealed to the researchers until the end of the study.

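### Section 2.1 makes more than 80,000 functional platelets a condition of randomisation, but sections 2.3, 2.7 and 2.8 describe randomising eligible patients without that condition

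*Protocol article*

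**What the plan says.** All places are in the protocol article.

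- Section 2.1 (Study design) puts the test before randomisation and makes its result the condition: "those with more than 80,000 functional platelets will be randomized to either early surgery with neuraxial anesthesia or delayed surgery with neuraxial anesthesia".
- Sections 2.3.2 and 2.3.3 (Inclusion and Exclusion criteria) require age, a femoral fracture and "receiving treatment with antiplatelet agents" at admission. The exclusions are multiple or pathological fractures, certain anticoagulants and coagulopathy. No functional platelet count appears in either list.
- Section 2.7 (Implementation and data collection) runs from eligibility check to information, consent and enrolment, and then: "Next, they will be randomized to one of the 2 study groups". No test result comes in between.
- Section 2.8.1 (Experimental intervention) places the admission test inside the experimental arm and provides for a low result: "if the level of functional platelets is <80,000, then the platelet assay will be performed once per day for the next 2 days". It has a further branch for patients not normalised after 3 days.
- Section 2.8.2 (Control intervention) names one control test: "Platelet function will be determined the day before surgery but the results will not be revealed to the researchers" until the study ends.
- Section 2.6 (Blinding) says that, so that surgical timing is not influenced, "the investigators will be blinded to the platelet function status in the control group".

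**The concern.** The rule for who is randomised defines the trial population, and the article gives two rules.

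Under the gate in 2.1, everyone in the comparison is already known to exceed 80,000. The question is then whether operating early rather than waiting shortens time to surgery in such patients. Under 2.7 and 2.8, every eligible consenting patient is randomised. The question is then whether a strategy of testing and acting on the result shortens time to surgery compared with a fixed drug-specific wait. The second comparison includes patients who fail the test and may wait as long as controls.

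Population, estimand and expected mean difference all change with the reading. Blinding is affected too. A gate would tell investigators that each control exceeded the threshold at admission, which is the kind of knowledge that 2.6 sets out to keep from them. This matters in an open-label trial whose primary endpoint is the timing of surgery.

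**Working it through.** **Step 1. Set the sections against the two readings.**

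| Section | Fits a gate at >80,000? | Fits randomising all eligible patients? |
|---|---|---|
| 2.1 Study design | Yes, stated | No |
| 2.3.2–2.3.3 Criteria | No threshold listed | Yes |
| 2.7 Implementation | No test between consent and randomisation | Yes |
| 2.8.1 Experimental arm | No: low-result branches would have no patients at admission | Yes |
| 2.8.2 Control arm | No admission test named, though a gate needs one | Yes |
| 2.6 Blinding | In tension: the admission status of controls would be known | Compatible |

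Two points of precision. No sentence says outright that randomisation precedes any platelet result; this follows from 2.7, 2.8.1 and 2.8.2 taken together. Section 2.6 does not say who is randomised; it bears on the matter only because a gate works against its stated purpose. The aim at the end of the Introduction, a strategy that includes preoperative platelet testing compared with conventional delay, also fits the second reading.

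**Step 2. Does the sample size show which population was meant?** Inputs from section 2.9.1: SD 3.17 days, difference 1.5 days, two-sided alpha 0.05, power 0.80, 10% loss, equal arms.

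n per arm = 2 × [3.17 × (1.960 + 0.842) / 1.5]² = 70.1

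70.1 / 0.90 = 77.9, so 78 per arm and 156 in total.

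The stated figure reproduces. (Rounding up at each step gives 71, then 79 per arm and 158 in total.) The formula has no input for the share of patients above 80,000, so 156 fits either reading and settles nothing.

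**Step 3. What could the choice do to power?** Two-sample t test, SD 3.17, 70 evaluable per arm, two-sided 0.05:

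| Mean gain (days) | Power |
|---|---|
| 1.0 | 46% |
| 1.5 | 79% |
| 2.0 | 96% |

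The mean gain that applies depends on quantities the article does not give. Let f be the assumed share above 80,000 at admission, and let surgery take place at the stated limits (1 day after a passing test, or the drug-specific wait).

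- Gate, 3-day drug: gain 3 − 1 = 2.0 days; power 96%.
- All randomised, 3-day drug, f = 0.5, no gain in the rest: 0.5 × 2 = 1.0 day; power 46%.
- Same, but the rest normalise at the first daily retest and gain 1 day: 0.5 × 2 + 0.5 × 1 = 1.5 days; power 79%.
- All randomised, 3-day drug, f = 0.75, no gain in the rest: 0.75 × 2 = 1.5 days; power 79%.
- All randomised, 5-day drug, f = 0.5, no gain in the rest: 0.5 × 4 = 2.0 days; power 96%.

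The last line equals the gated 3-day case. The drug mix (3 to 10 days in 2.1) and the retest results matter as much as the gate, so the direction and size of any change in power are not determined by the document.

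**The case against.** The strongest reply is that 2.1 is a single overview clause in a condensed journal article. The stated aim, the criteria, 2.7 and both arm descriptions point the same way. The article refers to a full protocol, version 3, which is not shown, and the flowchart (Figure 1) is not in the text available. Either might show which rule the trial follows. This stands as an explanation of how the clause may have arisen. It does not remove the contradiction: the conflicting sentences are all affirmative statements in the same document, and no figure could make both true.

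Three stronger conclusions are tempting and are not supported:

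- *Blinding would be impossible under a gate.* The result withheld in 2.8.2 is the one taken the day before surgery, and it could still be withheld. A gate would reveal only that the admission value exceeded the threshold. It undermines the purpose of 2.6 without making that provision unworkable.
- *Centres are following different rules.* Nothing in the article shows that any centre has applied a gate, or that centres work from this article and not from the full protocol.
- *Randomising all patients leaves the trial underpowered.* The 46% figure needs the shortest waiting time, an assumed pass share of one half, and no gain in anyone who fails at admission, although 2.8.1 retests those patients daily for 2 days and operates within 24 hours of normalisation. Other admissible assumptions give 79% or 96%.

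**Conclusion.** The contradiction holds. Section 2.1 states a rule for who is randomised that cannot be reconciled with 2.3, 2.7, 2.8.1 and 2.8.2, and that works against the purpose of 2.6. The consequence is that the trial population and the question answered are not fixed by the document. This needs correcting before analysis.

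Most of the text fits randomising all eligible consenting patients, so 2.1 may be a wording error, but the text shown does not settle it. The size of the effect on power is undetermined. The 46% to 96% range rests on the plan's SD, 70 evaluable per arm, and assumed pass shares, drug durations and retest outcomes. It illustrates sensitivity and does not demonstrate a loss of power.

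**What to change.** 1. Reconcile the sections so that one rule for who is randomised, and when relative to the platelet test, appears throughout. If all eligible consenting patients are randomised, align the clause in 2.1. If the gate was intended, rewrite 2.3, 2.6, 2.7 and 2.8 to match. The sponsor has to say which it is; no view is taken here on the platelet threshold or on the timing of surgery.
2. State the target population and the estimand that follow from that rule.
3. Check, by centre, how the 81 patients already included were randomised. If practice differed, flag the patients concerned and run a sensitivity analysis with and without them.

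Cost: one clarifying amendment and a check of 81 records. The clarification itself does not require a change to the planned 156. Whether 156 is enough under the chosen rule cannot be judged without the share above 80,000 at admission, the drug mix and the retest results.
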